## Abstract

Malawi has a population of around 20 million people and is one of the world’s most economically deprived nations. Severe mental illness (largely comprising psychoses and severe mood disorders) is managed by a very small number of staff in four tertiary facilities, aided by clinical officers and nurses in general hospitals and clinics. Given these constraints, psychosis is largely undetected and untreated, with a median duration of untreated psychosis (DUP) of around six years. Our aim is to work with people with lived experience (PWLE), caregivers, local communities and health leaders to develop acceptable and sustainable psychosis detection and management systems to increase psychosis awareness, reduce DUP, and to improve the health and lives of people with psychosis in Malawi. We will use the UK Medical Research Council guidance for developing and evaluating complex interventions, including qualitative work to explore diverse perspectives around psychosis detection, management, and outcomes, augmented by co-design with PWLE, and underpinned by a Theory of Change. Planned deliverables include a readily usable management blueprint encompassing education and community supports, with an integrated care pathway that includes Primary Health Centre clinics and District Mental Health Teams. PWLE and caregivers will be closely involved throughout to ensure that the interventions are shaped by the communities concerned. The effect of the interventions will be assessed with a quasi-experimental sequential implementation in three regions, in terms of DUP reduction, symptom remission, functional recovery and PWLE / caregiver impact, with quality of life as the primary outcome. As the study team is focused on long-term impact, we recognise the importance of having embedded, robust evaluation of the programme as a whole. We will therefore evaluate implementation processes and outcomes, and cost-effectiveness, to demonstrate the value of this approach to the Ministry of Health, and to encourage longer-term adoption across Malawi.

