Mental health services in Malawi are centralised in a Ministry of Health in-patient unit in Zomba (Southern region) and an outpatient clinic in Blantyre (Southern region), and St John of God Hospitaller Service facilities in Lilongwe (Central region) and Mzuzu (Northern region). Specialist mental health staff are scarce. Across the whole country there are four psychiatrists, three clinical psychologists, and seven social workers who are based in these four tertiary facilities [12]. Secondary care services in district hospitals are staffed by limited numbers of Mental Health Clinical Officers, who are clinical officers with additional degree level mental health training, and psychiatric nurses. Primary care is provided by general nurses, general clinical officers and medical assistants. District Mental Health Teams operating in district hospitals and outreach clinics are able to diagnose and treat psychosis, and screen for medical causes such as HIV/AIDS, malaria and cannabis use [14]. However, primary health care facilities in communities are staffed by non-specialist staff with limited capacity to diagnose and treat.

Most people in Malawi experiencing distress or unusual experiences/behaviours that would correspond to ICD/DSM diagnoses consult traditional or religious healers, and receive herbal or spiritual remedies. Combined with low accessibility of alternatives, people with possible ‘psychosis’ are frequently brought late to healthcare service attention. Consequently, it is only people with the most severe forms of psychosis that come to the attention of mental health professionals, such that the median DUP is estimated to be 71 months [15]. The vast majority of people with psychosis in Malawi do not receive either pharmacological or psychosocial interventions, with a likely adverse impact on outcome, caregiver burden and increased risk of adverse experiences including homelessness, accidents and assaults [4, 16].

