### Aims

The overarching goal of our research is to build on existing services and initiatives, to develop acceptable and sustainable psychosis detection systems and management pathways, and to improve outcomes for people with psychosis in Malawi. Our specific aims are:

1. To understand how perceptions and thoughts that would be recognised in diagnostic manuals as ‘psychosis’ are experienced and conceived of among people with lived experience (PWLE), caregivers, and HSAs in Malawi, and how these influence help-seeking and preferences for care;

2. To develop and validate a screening tool as part of a psychosis detection system in Malawi that is accurate, useful, and acceptable to PWLE, HSAs, and caregivers, and which facilitates engagement and reduces DUP;

3. To formalise a readily implementable psychosis management plan, emphasising community-level psychosocial interventions, with facility-based physical health care and receipt of antipsychotic medication, that is acceptable to PWLE, caregivers, HSAs and health workers;

4. To evaluate the implementation processes, effectiveness and cost-effectiveness of the psychosis detection and management system in improving outcomes prioritised by PWLE, caregivers, and health workers.

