#### Evaluating impact on service utilisation

We will conduct an interrupted time series study to evaluate the impact of the detection component (case-finding, diagnosis, referral, and engagement) of the psychosis detection and management system on service utilisation. Following the HSA screening assessment, people with probable psychosis will be referred to the appropriate facility in the care pathway, depending on severity. We will establish a simple, paper-based, case registration system in all the potential referral facilities, including private sector facilities, at least three months prior to initiating case-finding in that district. This will create sufficient baseline data time points in the pre-intervention period to allow us to assess levels of service utilisation for people with psychosis (new and existing) prior to the intervention and during the implementation of the detection system. This method has been used previously in Malawi to investigate the impact of an intervention on general mental health contacts with facilities [14]. We will use segmented linear regression using aggregated monthly utilisation data to assess whether the detection system leads to a significant increase in utilisation of each type of service beyond pre-intervention trends [39].

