#### Activities

*Intervention cohort study without controls / pre-post sequential group design*. The analysis of individual outcomes will use appropriate descriptive statistics to present the outcome in each district as well as the overall statistic for all three districts. The outcome data will be stratified by health equity indicators (sex, age category, urban/rural residence) and by drop outs and loss to follow up. A sample size of 150 will be sufficient to detect a pre-post improvement of 20% overall (across the four sub-scales) of the WHOQoL primary outcome measure with a power of 90% (alpha = 0.05). The data will have a three-level structure with repeated outcomes measures collected with individuals clustered within three separate assessment centres. It is reasonable to assume that different data from people with psychosis in the same centres will be correlated and measurements on the same person even more highly correlated. To handle this data structure we will use Mixed Models (including fixed effects and random latent effects) using the appropriate model for the distribution of outcome. For the continuous scaled primary outcome WHOQoL, a linear mixed effect model will model change before and after intervention to estimate mean difference as well as the moderating effects of key health inequity measures (gender, urban/rural residence, socio-economic status) and process indicators (e.g. engagement with facility-based and community-based interventions).

The final selection of outcome measures for the evaluation will be informed by PWLE of psychosis and other stakeholders, and Theory of Change roadmaps (ToC 1; ToC 2; ToC 3; ToC5) inclusive of agreed indicators of success. Quality of life is a valued outcome for both psychosocial interventions and antipsychotic medication, and is therefore the current proposed primary outcome measure. The range of potential measures are indicated in Table 5 below with outcome measures carried out at baseline (WP3) and at 6 and 12 months (WP 4). This allows for the incorporation of other measures prioritised by PWLE and other stakeholders, such as food insecurity [42], and will give enough time for participants to engage with the innovation to investigate feasibility, fidelity, cost-effectiveness and outcomes.

**Table 5 pone.0293370.t005:** WP4 anticipated outcome measures.

**Focus**	**Measure used to capture focus**	**Baseline (WP3)**	**6 months (WP4)**	**12 months (WP4)**
Primary outcome PWLE				

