Quality of life	WHOQoL	x	x	x
Health Economics				
Disability	DALYS (symptom data)	x	x	x
Quality of life	WHOQoL	x	x	x
Secondary outcome				
Duration of untreated psychosis	DUP	x	x	x
Symptom Severity	Positive and Negative Syndrome Scale (PANSS)	x	x	
Family Burden	Family Burden Interview Schedule (FBIS)	x	x	
Health and disability	WHO Disability Assessment Schedule (WHODAS)	x	x	

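### DUP reduction is a promised effect, but the only DUP data described are repeat measurements in one intervention-found cohort, where true DUP cannot fall, and no pre-intervention comparator is stated

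*Protocol article*

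**What the plan says.** The abstract puts DUP first among the effects to be evaluated: "The effect of the interventions will be assessed with a quasi-experimental sequential implementation in three regions, in terms of DUP reduction". The same sentence names quality of life as the primary outcome. Aim 2 describes a screening tool within a detection system "which facilitates engagement and reduces DUP".

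WP4, Activities, gives the design as "Intervention cohort study without controls / pre-post sequential group design", with "outcome measures carried out at baseline (WP3) and at 6 and 12 months (WP 4". In Table 5 the secondary-outcome row "Duration of untreated psychosis" is marked in all three columns: baseline, 6 months and 12 months. The table is titled as anticipated measures, and the text says the final selection will follow stakeholder input.

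On analysis, WP4 states: "The data will have a three-level structure with repeated outcomes measures collected with individuals clustered within three separate assessment centres". Mixed models are to handle this structure. The explicit before-and-after model is written for WHOQoL.

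The only DUP figure is background from a cited source (Introduction): "the median DUP is estimated to be 71 months". The only comparison with a pre-intervention period is the interrupted time series in WP3 (Evaluating impact on service utilisation), which uses "segmented linear regression using aggregated monthly utilisation data". DUP is not mentioned there.

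**The concern.** Early detection shortens DUP by changing who comes to treatment and how soon. The effect shows up between people: cases first treated after the system starts should have waited less than comparable cases first treated before it. It does not show up within a person followed from the moment of detection, because that person's untreated time has already been spent.

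Table 5 treats DUP like a symptom or quality-of-life score, something with a before and an after value in the same individual. If it is analysed that way, the result is no change or an increase however well detection works. A named aim would go unanswered, and a successful programme could appear to have failed on it.

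The timing matters too. Pre-intervention DUP can be collected prospectively only while the facility registers are open and case-finding has not begun in that district.

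**Working it through.** **Inputs.** From the article: assessments at 0, 6 and 12 months; one cohort without controls; anticipated cohort size 150; background median DUP 71 months. The article does not define DUP, so I assume its plain meaning, time from onset of psychosis to start of treatment.

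**The article's own figure.** 71 / 12 = 5.92 years, which agrees with the abstract's figure of around six years. No sample size or power is stated for DUP, so there is nothing further to reproduce.

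**The bound.** Let O be the onset date, T the date of first treatment and t the assessment date. The DUP accrued by t is

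DUP(t) = min(T, t) − O.

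As t increases, min(T, t) either rises or stays where it is, so DUP(t) never decreases. With baseline at t = 0, the change to month m is

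Δ(m) = min(T, m) − min(T, 0).

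- Treated by baseline (T ≤ 0): Δ(m) = T − T = 0.
- Treated between baseline and m: Δ(m) = T, which lies between 0 and m.
- Still untreated at m: Δ(m) = m, that is +6 at month 6 and +12 at month 12.

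So 0 ≤ Δ(6) ≤ 6 and 0 ≤ Δ(12) ≤ 12 months for every participant.

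**Illustrative averages.** Suppose a proportion p is already treated at baseline and the rest wait an exponentially distributed time with mean θ. Both are assumptions, since the article gives neither. The expected change is (1 − p) × θ × (1 − e^(−m/θ)). For p = 0.3, θ = 12, m = 12 this is 0.7 × 12 × (1 − e^(−1)) = 0.7 × 12 × 0.632 = 5.31 months. The last column comes from one simulated cohort of 150 with lognormal baseline DUP, median 71 months.

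| Already treated | Mean wait (months) | Expected change, month 6 | Expected change, month 12 | Simulated change, month 12 |
|---|---|---|---|---|
| 100% | n/a | 0 | 0 | 0 |
| 30% | 3 | +1.82 | +2.06 | +2.42 |
| 0% | 3 | +2.59 | +2.95 | +2.88 |
| 30% | 12 | +3.31 | +5.31 | +5.51 |

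No simulated participant showed a fall. The sizes depend on the assumptions; the sign does not.

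**Is there another stated comparison?** I looked for one in three places.

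1. The cohort itself. Under WP3 (Validation study), possible cases come from community awareness-raising and trained HSAs, so the cohort contains no group identified before the intervention.
2. The interrupted time series. It has a pre-intervention period, but its outcome is monthly service use.
3. The 71-month median. It is cited as background and not named as a comparator. It describes people who reached services late under existing care, a differently selected group from cases found in the community.

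None of these supplies a DUP contrast.

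**The case against.** The strongest reply is that a within-person DUP analysis is inferred. The before-and-after model is spelled out only for WHOQoL, Table 5 is provisional, and a fuller protocol or analysis plan could treat this secondary outcome differently. That stands as a limit on wording: the article does not say outright that DUP will be analysed as change from baseline. It does not remove the mismatch. The claimed effect and the measurement schedule are both in print, they do not fit together, and an analysis plan cannot supply pre-intervention DUP data that were never collected.

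Second, the follow-up marks may have a proper use. A person untreated at baseline has a censored DUP, and a later visit is needed to learn when treatment began. This stands. A reader might infer that DUP should simply be removed from the 6- and 12-month columns; doing so would lose those treatment-start dates.

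Third, the words sequential group in the design label might be read as a comparison of successive groups of new cases. The article describes no such comparison for DUP, and the analysis paragraph describes repeated measures on the same people.

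Two stronger readings are also tempting. One is that an observed fall has zero probability. That holds for true DUP, not for recorded DUP: if onset is asked again at each visit, recall error can produce apparent falls. The other is that case-finding will push observed DUP upwards by drawing out a backlog of long-untreated people. This is plausible given the 71-month median, but the article gives no DUP distribution for community-found cases, so the direction is not established.

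**Conclusion.** The point holds in limited form. As published, the plan cannot show the DUP reduction it promises. True within-person change is bounded below by zero and above by 6 months at month 6 and 12 months at month 12, and no pre-intervention DUP comparator is stated. The conclusion rests on the plain meaning of DUP and on the article's own schedule and design; it needs no assumption about waiting times.

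A reader might go further and infer that the study could never measure an effect on DUP, or that the evaluation as a whole is undermined. The documents support neither. A comparison of first-treated cases before and after case-finding could show a reduction; it is just not described. DUP is secondary, and the WHOQoL analysis, the validation study and the service-use time series do not depend on it. This should be fixed, and before the registers open, but it does not threaten the primary result.

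**What to change.** 1. Define DUP as one value per person, from onset to first treatment, and say what counts as each. Fix the onset date at baseline. Use the 6- and 12-month visits only to capture the treatment-start date in people still untreated, with those never treated censored. Do not analyse the visits as repeated DUP outcomes.
2. Add onset date and first-treatment date to the facility case register before it opens in each district. The article already plans to open it at least three months ahead of case-finding.
3. Compare DUP among first-treated cases before and after case-finding starts, by district and calendar time, on medians or log-DUP. The district-by-district roll-out in WP3 gives staggered start dates for this.
4. Report recent-onset cases separately, with the cut-off set in advance (24 months is one illustrative choice), because case-finding could at first bring in long-untreated people and raise observed DUP.
5. If this is not feasible, drop DUP reduction from the list of assessed effects and report DUP as a baseline descriptor or moderator.

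The cost is two dates on a form that is being created anyway, plus protocol wording. The weaknesses should be stated: recalled onset dates are noisy, and a three-month pre-period may yield few first-treated cases, so the comparison may be imprecise.

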## Introduction

Psychoses–principally schizophrenia and related conditions, including affective psychosis–can be experienced as deeply distressing and disabling conditions. Around 50% of people with psychosis in High Income Countries (HICs) will have ongoing symptoms and social and occupational functioning difficulties (APA, 2013). In one particularly comprehensive study, conducted in Finland, the combined lifetime risk of all psychoses was around 3%, with a prevalence of 1% [1]. The global point prevalence of schizophrenia is estimated to be 0.3–0.6% [2, 3].

Duration of untreated psychosis (DUP) is a key issue of clinical and public health concern. A longer DUP of even a few weeks or months has been consistently linked to worse outcomes in terms of more severe symptoms, worse social, vocational, and overall functioning, and reduced quality of life. This has been reported in many countries around the world, including low- and middle-income countries (LMICs) within Africa [4, 5]. The most cost-effective interventions for schizophrenia in Nigeria include community-based treatment with older antipsychotic drugs plus psychosocial support or case management [6]. Clinical trials indicate that antipsychotic drug treatment leads to quicker symptom relief, reduces the risk of relapse, and probably improves quality of life [7], and that psychosocial interventions such as illness education and support reduce relapse risk [8]. Notably, however, antipsychotic drugs can have unpleasant adverse effects which reduce their acceptability [9].

Malawi is a sub-Saharan African country with approximately 15 million people under the age of 30. No studies of the prevalence of psychosis generally or schizophrenia in Malawi have been conducted, but the increased risk of schizophrenia among the young and those living in poverty [10] are reasons to think it may be higher than in HICs. The prevalence of HIV/AIDS, malaria, and cannabis use [11, 12] could mean that organic and substance-induced psychoses are particularly common. Epidemiological surveys also suggest that brief psychoses could be more common in LMICs such as Nigeria than HICs [13].

Mental health services in Malawi are centralised in a Ministry of Health in-patient unit in Zomba (Southern region) and an outpatient clinic in Blantyre (Southern region), and St John of God Hospitaller Service facilities in Lilongwe (Central region) and Mzuzu (Northern region). Specialist mental health staff are scarce. Across the whole country there are four psychiatrists, three clinical psychologists, and seven social workers who are based in these four tertiary facilities [12]. Secondary care services in district hospitals are staffed by limited numbers of Mental Health Clinical Officers, who are clinical officers with additional degree level mental health training, and psychiatric nurses. Primary care is provided by general nurses, general clinical officers and medical assistants. District Mental Health Teams operating in district hospitals and outreach clinics are able to diagnose and treat psychosis, and screen for medical causes such as HIV/AIDS, malaria and cannabis use [14]. However, primary health care facilities in communities are staffed by non-specialist staff with limited capacity to diagnose and treat.

Most people in Malawi experiencing distress or unusual experiences/behaviours that would correspond to ICD/DSM diagnoses consult traditional or religious healers, and receive herbal or spiritual remedies. Combined with low accessibility of alternatives, people with possible ‘psychosis’ are frequently brought late to healthcare service attention. Consequently, it is only people with the most severe forms of psychosis that come to the attention of mental health professionals, such that the median DUP is estimated to be 71 months [15]. The vast majority of people with psychosis in Malawi do not receive either pharmacological or psychosocial interventions, with a likely adverse impact on outcome, caregiver burden and increased risk of adverse experiences including homelessness, accidents and assaults [4, 16].

These limits to the capacity of existing health services in Malawi to provide care for people with psychosis and their families form the rationale for our research. It’s feasibility, in turn, relates to several notable strengths and initiatives within Malawi. These include the many researchers and institutions collaborating on this project, but crucially Health Surveillance Assistants (HSAs). These are secondary school graduates trained in health, located throughout Malawi at the village level, and primarily tasked with managing TB and HIV/AIDS. They typically serve a 1,000–2,000 population, and 10–20 HSAs are affiliated with each Primary Care Health Centre. In April 2020, the Ministry of Health launched a new policy to improve access to integrated quality mental health services, including training HSAs in mental health. We, therefore, plan to train HSAs to identify possible psychosis, use referral pathways, and provide community-based brief psychosocial interventions.

